### Measurement timings and study end points

At the trial consultation, all participants will be fully informed about trial follow-up procedures. The participant-reported measures (numbers 1–8 above) are completed in person at baseline, and online at follow-up 1 (6 months) and follow-up 2 (12 months), with the exception of the skin symptom questionnaire as already described, which is sent to participants by postal mail within a month of any consultation for skin changes or pigmented skin lesions.

After trial completion, a final audit of the GP electronic medical records will be run to identify all skin consultations for the 12 months during the trial as well as the previous 12 months. Melanoma incidence findings will also be collected at the end of the 12-month follow-up period and at 5 years. These data will not be collected for participants who formally withdraw from the trial.

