### Outcomes and measures

The primary outcomes of this trial are *consultation rates* for pigmented skin lesions and the *patient interval.* C*onsultation rates* for changes to an existing pigmented skin lesion or concerns about a new pigmented skin lesion for 12 months before the trial and 12 months after the trial consultation will be collected via searching general practice electronic medical records using a clinical notes audit for every participant. The *patient interval* is the time from first noticing a skin change to first consultation. These data will be collected monthly by searches of general practice electronic medical records for all skin changes or pigmented skin lesions presented to their general practitioner (GP) or practice nurse during the 12 months following the trial consultation. When a participant consults about a pigmented skin lesion, they receive a skin questionnaire to complete. This skin questionnaire uses the symptom study instrument modified for melanoma symptoms. The instrument is a participant-completed questionnaire collecting data on symptoms and their duration prior to consultation, validated in prospective studies examining symptom and patient factors associated with longer time to diagnosis for colorectal, lung and pancreatic cancer.^25–27^ The skin questionnaire comprises 10 items starting with a free text response to ‘What was the first skin change or mole you noticed that made you think something might be wrong?’ Each item includes the subitems: ‘When did you first notice this?’ and ‘When did you first tell your GP or nurse?’

Secondary measures and outcomes (measured at baseline, 6 and 12 months) include:
*demographics and clinical variables:* age, gender, marital status, postcode, highest education level, occupation, history of skin cancer (melanoma, squamous cell carcinoma, basal cell carcinoma), skin and hair type (density of freckles on arms before age 20, natural hair colour at age 15, number of severe sunburns aged 2–18), number of raised moles on both arms, measured at baseline only,^21 22^ collected as part of the baseline eligibility assessment;

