### Statistical analysis

All randomised patients will be considered eligible for inclusion in the analysis in accordance with the intention-to-treat analysis principle. As this is a phase II trial, fully describing and characterising the extent and nature of the missing data is an important part of the analysis. For the outcome analysis, appropriate methods for dealing with missing endpoint data will be informed by a blinded review of the data; however, assuming that this is appropriate, we plan a series of extreme case-sensitivity analyses, where missing data will be replaced with the 2.5th and 97.5th centiles of the non-missing measured outcomes to assess the maximum potential impact on the results of the trial. The baseline characteristics of the two arms will be described using summary statistics. Possible consent bias will be assessed by comparing demographic and clinical variables of participants with those who declined participation, and possible differential attrition will be assessed by comparing baseline characteristics of those who withdraw or die with those who remain in the trial. In addition, we will analyse the missing data to understand the potential impact on the required sample size, and to assess whether and where possible bias may arise, and therefore be minimised, in the future design for the efficacy phase III trial. We will describe the amount (percentage) of missing data in all outcome measures at baseline and follow-up, and evaluate the relationship between missing data and treatment assignment using unadjusted Χ^2^ tests. We will describe whether missing data occur differentially between outcomes. These comparisons will be performed using a two sample t test (or non-parametric equivalent) for continuous variables and Χ^2^ test for categorical variables.

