The primary analysis will be a comparison between the two groups on the consultation rate for skin changes/pigmented skin lesion using a Poisson regression model. Comparisons between groups on binary secondary endpoints will be performed using logistic regression. Comparisons between groups on continuous secondary endpoints will be undertaken using a linear model that includes the baseline value where applicable. A linear model may not be appropriate for the secondary outcome patient interval, as this is expected to be right skewed.^36^ We will explore the nature and extent of the skewness and analyse patient interval using a linear model if possible, adopting other approaches as appropriate, including transformation or categorisation of the patient interval, or methods for statistical inference based on bootstrap resampling. The analyses performed on the primary and secondary endpoints will be repeated adjusting for additional baseline covariates as part of a sensitivity analysis. Point estimates of the intervention effect will be presented with 95% CIs and two-sided P values. Unadjusted P values from secondary analyses will be interpreted in proper context and be clearly labelled.

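### The GP-record audit behind the primary consultation rate is not to be run for formal withdrawers, which loses passively recorded outcome data that an intention-to-treat analysis needs

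*Protocol article*

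**What the plan says.** Under Outcomes and measures, consultation rates for the 12 months before and the 12 months after the trial consultation "will be collected via searching general practice electronic medical records using a clinical notes audit for every participant". The same section describes monthly record searches during follow-up, which serve the patient interval.

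Under Measurement timings and study end points, the plan once follow-up has ended is that "a final audit of the GP electronic medical records will be run to identify all skin consultations for the 12 months during the trial", and also for the preceding 12 months. Next comes a sentence on melanoma incidence at 12 months and 5 years. The paragraph then closes: "These data will not be collected for participants who formally withdraw from the trial".

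Under Statistical analysis, "All randomised patients will be considered eligible for inclusion in the analysis in accordance with the intention-to-treat analysis principle". The primary analysis is fixed there: "The primary analysis will be a comparison between the two groups on the consultation rate for skin changes/pigmented skin lesion using a Poisson regression model". That section also plans to "evaluate the relationship between missing data and treatment assignment using unadjusted" chi-squared tests, to check differential attrition by "comparing baseline characteristics of those who withdraw or die with those who remain in the trial", and to run sensitivity analyses in which "missing data will be replaced with the 2.5th and 97.5th centiles of the non-missing measured outcomes". The main method for missing endpoints is left to a blinded review of the data.

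**The concern.** Consultations are recorded in the practice whether or not a participant stays engaged with the trial. Non-collection after withdrawal is therefore, to a large extent, a consequence of the protocol's own rule and not of the outcome being unobtainable. The rule also discards the prior-year counts, which precede randomisation and cannot be affected by it.

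The loss depends on something that happens after allocation. Only the intervention arm has App loading, photography and monthly reminders. In the pilot described in the article, several users found photography difficult, and most reported sometimes worrying about skin cancer and, among other responses, visiting their practice. A link between burden, worry, leaving the trial and consulting is thus plausible, though not shown. If it exists and differs by arm, the comparison of those who remain is not the comparison that was randomised.

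The trial is also meant to supply attrition, data-completeness and effect-size figures for sizing phase III. Avoidable loss makes completeness of the record-based outcome look worse than the method can deliver.

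**Working it through.** **The text.** One section promises the record audit for all participants, and another withdraws it for a subgroup defined after randomisation. The two cannot both be followed. Grammatically, the closing sentence could refer to melanoma incidence alone, since that sentence comes immediately before it. But the paragraph is about the final audit and the incidence collection together, so the natural reading covers both.

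**The plan's own figure.** Sample size consideration gives 1600 × 0.25 = 400 eligible and 400 × 0.50 = 200 randomised. The target of 200 reproduces. Allocation is 1:1, so about 100 per arm.

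**Primary data lost.** The article gives no withdrawal rate, so a range is assumed. Participants retained = 200 × (1 − w):

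| Assumed w | Lost | Retained |
|---|---|---|
| 2% | 4 | 196 |
| 5% | 10 | 190 |
| 10% | 20 | 180 |
| 15% | 30 | 170 |
| 20% | 40 | 160 |

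**Possible bias, true rate ratio 1.0.** Assume an overall rate of 0.20 a year in both arms and a rate r_w among withdrawers. The observed rate in an arm is (0.20 − w × r_w)/(1 − w). All inputs are assumptions.

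- 10% v 2% (App v control), r_w = 0.05: (0.195/0.90)/(0.199/0.98) = 0.2167/0.2031 = 1.07
- 10% v 2%, r_w = 0.5: (0.150/0.90)/(0.190/0.98) = 0.1667/0.1939 = 0.86
- 15% v 3%, r_w = 0.05: (0.1925/0.85)/(0.1985/0.97) = 0.2265/0.2046 = 1.11
- 15% v 3%, r_w = 0.5: (0.125/0.85)/(0.185/0.97) = 0.1471/0.1907 = 0.77

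**A second form.** Let k be the withdrawers' rate relative to stayers, the same in both arms. The observed ratio is [(1 − d_C) + d_C k]/[(1 − d_I) + d_I k], where d_I and d_C are the withdrawal proportions in the App and control arms.

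- Equal withdrawal: 1.00 for any k, so data are lost without distortion.
- 10% v 3%: 0.97/0.90 = 1.08 at k = 0; 1.06/1.20 = 0.88 at k = 3.
- 20% v 5%: 0.95/0.80 = 1.19 at k = 0; 1.10/1.40 = 0.79 at k = 3.

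**Comparison with sampling error.** At 0.20 a year and 100 per arm, about 20 events are expected per arm. The standard error of the log rate ratio is √(1/20 + 1/20) = 0.32, so a 95% interval around 1.0 is about 0.54 to 1.86.

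**What the planned centile replacement does.** For Poisson counts with an assumed mean of 0.1 to 0.2, the 2.5th and 97.5th centiles are 0 and 1. Take 10% v 3% missing and equal rates in those observed.

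- All missing set to 0: 0.90/0.97 = 0.93.
- All set to 1, mean 0.2: (0.18 + 0.10)/(0.194 + 0.03) = 1.25.
- All set to 1, mean 0.1: (0.09 + 0.10)/(0.097 + 0.03) = 1.50.

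These replacements bracket the problem coarsely; they do not recover the counts.

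**The case against.** Several points on the other side are sound.

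- **Scope of the rule.** A reader might infer that anyone who stops the App or skips questionnaires drops out of the audit, making the primary analysis a completers' comparison. The text does not support this. The rule is confined to formal withdrawal from the trial, and non-users and non-responders are not stated to be excluded.
- **Differential withdrawal.** A reader might also infer that withdrawal is likely to be heavier in the App arm. The article gives no withdrawal rate, overall or by arm. App burden can be escaped without formally withdrawing, and both arms complete the same follow-up questionnaires.
- **Intention-to-treat.** Being eligible for inclusion does not promise complete data, so the principle is weakened, not strictly contradicted. The direct textual conflict is with the audit of all participants.
- **Size.** The illustrated shifts lie well inside sampling error, and the article disclaims firm clinical conclusions from so small a trial.
- **Existing safeguards.** The missing-data description, the checks by arm and the sensitivity analyses are useful. Centile replacement is planned only as a sensitivity analysis.
- **Unseen documents.** The consent form and any analysis plan may define levels of withdrawal and the use of data already held. Where someone refuses record access, non-collection is proper.

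What remains is that the article does not merely leave this open. It states a rule of non-collection, and no later analysis can restore outcomes that could have been read from the record.

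**Conclusion.** The point holds as a fault of moderate weight that should be corrected. Followed as written, the rule discards the primary outcome and the prior-year counts for every formal withdrawer, against the article's own promise of a complete audit. How many are affected is unknown: 2% to 20% withdrawal would mean 4 to 40 of 200.

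Bias requires that withdrawal be related to consulting and that its extent, or the kind of person who withdraws, differ between arms. Neither condition can be established from the article. Under the assumed 10% v 2% withdrawal and a true ratio of 1.0, the observed ratio would lie between about 0.86 and 1.07, in either direction. The planned missing-data analyses mitigate this only in part. The conclusion also rests on reading the closing sentence as covering the audit; if melanoma incidence alone was meant, the wording needs clarifying.

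**What to change.** Replace the blanket rule. Run the audit, for both the trial year and the prior year, for every randomised participant unless that person refuses access to the record, and ask this explicitly at formal withdrawal. State that stopping the App or not returning questionnaires is not withdrawal from record follow-up.

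For those who refuse access, keep consultations already found by the monthly searches up to the withdrawal date, where consent allows. Include log(person-time) as an offset in the Poisson model so that partial follow-up counts for its length. The offset does not correct for a change in consulting after withdrawal, so the planned sensitivity analyses remain worthwhile for this smaller group. State also which data the closing sentence of the paragraph refers to.

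The cost is one extra question to withdrawers, revised wording in the protocol and analysis plan, and ethics notification. Because enrolment closed on 6 January 2017 and consents were already signed, data for those who have already withdrawn may not be recoverable.

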### Participant data and study management

All participants are allocated a unique identifying code. Melanoma risk assessment data, baseline questionnaire and follow-up questionnaires data are stored on a custom built database on a secure server hosted by the Outcome Registry Intervention and Operation Network, Clinical Neurosciences Department at the University of Cambridge.

### Sample size consideration

Based on our recent MelaTools Q study with an identical screening step (response rate of 86%), we anticipate that we will need to approach approximately 2000 people from 10 general practice waiting rooms for about 1600 to complete the Melatools Q risk assessment tool.^23^ About 25%, 400 people, will be identified as increased risk and be eligible to participate in the trial. Based on previous research, we would expect approximately 50% of these to attend their trial consultation and undergo randomisation in order to reach our target of 200 participants.

We will use information on recruitment, attrition and data completeness, and preliminary estimates of effect sizes where appropriate, to inform the sample size calculation for a future phase III trial.

### Statistical analysis

All randomised patients will be considered eligible for inclusion in the analysis in accordance with the intention-to-treat analysis principle. As this is a phase II trial, fully describing and characterising the extent and nature of the missing data is an important part of the analysis. For the outcome analysis, appropriate methods for dealing with missing endpoint data will be informed by a blinded review of the data; however, assuming that this is appropriate, we plan a series of extreme case-sensitivity analyses, where missing data will be replaced with the 2.5th and 97.5th centiles of the non-missing measured outcomes to assess the maximum potential impact on the results of the trial. The baseline characteristics of the two arms will be described using summary statistics. Possible consent bias will be assessed by comparing demographic and clinical variables of participants with those who declined participation, and possible differential attrition will be assessed by comparing baseline characteristics of those who withdraw or die with those who remain in the trial. In addition, we will analyse the missing data to understand the potential impact on the required sample size, and to assess whether and where possible bias may arise, and therefore be minimised, in the future design for the efficacy phase III trial. We will describe the amount (percentage) of missing data in all outcome measures at baseline and follow-up, and evaluate the relationship between missing data and treatment assignment using unadjusted Χ^2^ tests. We will describe whether missing data occur differentially between outcomes. These comparisons will be performed using a two sample t test (or non-parametric equivalent) for continuous variables and Χ^2^ test for categorical variables.

The primary analysis will be a comparison between the two groups on the consultation rate for skin changes/pigmented skin lesion using a Poisson regression model. Comparisons between groups on binary secondary endpoints will be performed using logistic regression. Comparisons between groups on continuous secondary endpoints will be undertaken using a linear model that includes the baseline value where applicable. A linear model may not be appropriate for the secondary outcome patient interval, as this is expected to be right skewed.^36^ We will explore the nature and extent of the skewness and analyse patient interval using a linear model if possible, adopting other approaches as appropriate, including transformation or categorisation of the patient interval, or methods for statistical inference based on bootstrap resampling. The analyses performed on the primary and secondary endpoints will be repeated adjusting for additional baseline covariates as part of a sensitivity analysis. Point estimates of the intervention effect will be presented with 95% CIs and two-sided P values. Unadjusted P values from secondary analyses will be interpreted in proper context and be clearly labelled.

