## Methods and analysis

### Study design and setting

The phase II trial is a multisite randomised controlled trial (figure 2), set in 11 general practices across Eastern England. Those who meet the eligibility criteria and consent to participate are randomised 1:1 into either the control or intervention group. Randomisation is being performed using an online system provided by the Clinical Trials Unit based at Kings College London.

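### The differential-attrition check leaves out arm, so it cannot say in which arm selective dropout arises and can miss opposing patterns

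*Protocol article*

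**What the plan says.** All the relevant text is in the Statistical analysis section of the protocol article.

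- **Attrition:** "possible differential attrition will be assessed by comparing baseline characteristics of those who withdraw or die with those who remain in the trial".
- **Test:** "These comparisons will be performed using a two sample t test (or non-parametric equivalent) for continuous variables", with a chi-squared test for categorical variables. This sentence stands a little way below the attrition sentence, but the natural reading is that it covers the comparisons of baseline characteristics.
- **By-arm check:** the authors will "evaluate the relationship between missing data and treatment assignment using unadjusted" chi-squared tests.
- **Baseline by arm:** "The baseline characteristics of the two arms will be described using summary statistics". Nothing says that this will be split by leaver or stayer.
- **Purpose:** the missing-data work is meant "to assess whether and where possible bias may arise, and therefore be minimised, in the future design for the efficacy phase III trial".

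No sentence compares leavers with stayers within an arm, compares the arms among completers, or brings arm and baseline characteristics together in a model of dropout.

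**The concern.** Attrition distorts a randomised comparison when the arms lose different kinds of participants, even if they lose the same number. The comparison that the plan labels as differential attrition has two groups, leavers and stayers. It describes how representative the completers are of everyone randomised. The chi-squared tests against assignment bring in arm but look only at frequency. Between them, the two checks do not ask who left which arm.

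The question is a live one here. Only the intervention group is given the App, instruction in its use and monthly reminders (Intervention group); controls receive leaflets (Control and intervention groups and randomisation). Several pilot users found the photography hard (Piloting the intervention). People could leave the two arms for different reasons. What is at stake is mainly the feasibility report: it could state that no differential attrition was seen, or that some was, on evidence that does not bear on the arms, and so mislead the phase III design.

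**Working it through.** **1. The plan's own figure.** Sample size consideration: 1,600 x 0.25 x 0.50 = 200, which reproduces the target ("undergo randomisation in order to reach our target of 200 participants"). Study design and setting has participants "randomised 1:1 into either the control or intervention group", so about 100 per arm. The article gives no expected attrition rate and no size for any leaver-stayer difference. The 10%, 20% and 30% attrition rates and the SD differences below are assumptions.

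**2. What each comparison estimates.** Let dA and dC be the mean leaver-minus-stayer difference, in SD units, in the App and control arms. With equal arms and equal attrition, the pooled comparison estimates (dA + dC)/2. Attrition that differs by arm is dA - dC. At 20% attrition there are 20 leavers and 80 stayers per arm:

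- pooled SE = sqrt(1/40 + 1/160) = 0.1768
- leaver-by-arm SE = sqrt(1/20 + 1/80 + 1/20 + 1/80) = 0.3536

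Expected z values:

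- Opposing (+0.5, -0.5): pooled 0/0.1768 = 0; leaver-by-arm 1.0/0.3536 = 2.83.
- Shared (0.5, 0.5): pooled 0.5/0.1768 = 2.83; leaver-by-arm 0/0.3536 = 0.
- One arm only (0.8, 0): pooled 0.4/0.1768 = 2.26; leaver-by-arm 0.8/0.3536 = 2.26.

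The pooled test responds to the sum of the two patterns; the question about arms concerns their difference.

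**3. Simulation.** 4,000 runs per scenario, 100 per arm, equal attrition in both arms, two-sided 5% level. Entries are the percentage of runs flagged.

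| Pattern | Attrition per arm | Pooled t test | Chi-squared by arm | Leaver-by-arm |
|---|---|---|---|---|
| Opposing, +0.5 and -0.5 SD | 10% | 6.2 | 4.9 | 54.4 |
| | 20% | 5.8 | 6.0 | 78.6 |
| | 30% | 5.5 | 5.1 | 88.9 |
| One arm only, 0.8 SD | 10% | 39.1 | 5.0 | 38.6 |
| | 20% | 59.2 | 5.1 | 60.9 |
| | 30% | 70.3 | 5.8 | 72.4 |
| Shared by both arms, 0.5 SD | 10% | 54.1 | 5.3 | 5.0 |
| | 20% | 80.0 | 5.6 | 5.7 |
| | 30% | 89.1 | 5.5 | 5.3 |

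For opposing patterns, both planned checks stay near their 5% false-positive rate. For a pattern in one arm, the pooled test has about the same power as the leaver-by-arm test, but a positive result looks the same as one from a shared pattern. For a shared pattern, the pooled test signals although nothing differs between the arms.

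**4. The same on a scale (assumed values).** Take 100 per arm, baseline anxiety mean 7 in both, and 20 leavers per arm averaging 9 (App) and 5 (control).

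- App completers: (700 - 180)/80 = 6.5
- Control completers: (700 - 100)/80 = 7.5
- Pooled leavers: (180 + 100)/40 = 7
- Pooled stayers: (520 + 600)/160 = 7
- Missingness: 20/100 = 20% in each arm

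Both planned checks show nothing, yet the completers differ by 1 point at baseline.

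**The case against.** **The text is silent rather than wrong.** The article does not say that the arms will be pooled. A two-sample test can be run within each arm, and Data monitoring refers to an analysis plan that is not shown. That plan may well split the table. Even so, the article does more than omit a detail: it names the quantity and the comparison meant to assess it, and arm is absent from that comparison.

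**It may be only a label.** The same sentence assesses consent bias by comparing participants with decliners, so the attrition comparison can be read as the next step in asking who is lost. On that reading it is a sound check on representativeness and should stay. It still leaves the by-arm question unasked.

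**A reader might infer that the planned checks are blind to differential attrition.** They are not. Differing rates of loss are covered by the chi-squared tests. A one-arm pattern can show in the pooled test (59.2% of runs at 0.8 SD and 20% attrition), where the interaction test does no better. Near-null results on both checks need opposing patterns, and complete cancellation is a special case that nothing in the article predicts.

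**A reader might also infer that the trial's effect estimates would be biased.** The article does not support that either. Continuous endpoints are modelled with the baseline value where applicable, the analyses are repeated with further baseline covariates, and extreme-case sensitivity analyses are planned. In the anxiety example, the 1-point gap would be adjusted for in the anxiety outcome. Consultation rates come from practice records, so questionnaire non-response does not remove them, although Measurement timings and study end points suggests that formal withdrawal may.

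**The interaction test is weak.** At 0.5 SD in one arm and 20% attrition, z = 0.5/0.3536 = 1.41, or about 29% power. Across many baseline variables it would yield much noise. This stands, and is why the table should lead.

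**Conclusion.** The point holds in a limited form. The stated comparison does not fully serve its stated purpose: it cannot attribute selective dropout to an arm, cannot separate a shared pattern from a one-arm pattern, and can miss opposing ones. Under the assumed opposing 0.5 SD patterns, the two planned checks flag 4.9% to 6.2% of runs across 10% to 30% attrition, against 54.4% to 88.9% for a leaver-by-arm comparison. Under a shared 0.5 SD pattern, the pooled test flags 54.1% to 89.1%.

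These figures rest on assumed attrition rates and differences, equal attrition in the two arms, and about 100 per arm. The structural point, that the pooled contrast follows the sum and not the difference of the arm patterns, does not depend on the particular values chosen. Importance is minor: this is a feasibility trial that expects no significant clinical conclusions. It merits a change because locating possible bias for phase III is a declared aim of the missing-data work.

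**What to change.** In the Statistical analysis section, or in the analysis plan that the steering committee approves:

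- Make the main assessment of differential attrition a table of baseline characteristics of leavers and stayers within each arm, with a companion table of completers by arm.
- Add an arm-by-baseline term in a logistic model of dropout as exploratory support only, since leavers may be few among 200 participants.
- Keep the pooled leaver-stayer comparison, described as a check on how representative the completers are.
- Keep the chi-squared tests against assignment, described as a check on rates of loss.

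The adjusted sensitivity analyses already planned can accommodate predictors of dropout, so the outcome models need no change. The cost is one extra set of tables and one exploratory model, from data already collected. The drawback is low power for the interaction, so a null result there should not be read as showing that the arms lost the same kinds of participants.
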